## Abstract

**Background:**

More than one-third of German students report high emotional exhaustion. One effective and low-cost method for improving emotional well-being is journaling, and advances in artificial intelligence (AI), particularly in Natural Language Processing (NLP), enable automated analysis of journal content for mental health monitoring. These analyses can be returned to users as personalized feedback, thereby enhancing the positive effects of journaling through increased self-reflection and creating an incentive for continuous use, which, in turn, improves monitoring. Journaling apps offer various input modalities (e.g., typing, speaking), potentially further increasing participation. Despite the promising potential of AI-powered journaling apps, their effects on mental health have so far been scarcely investigated.

**Research question:**

This study investigates the performance of NLP models in predicting emotional well-being from journal entries. Specifically, it examines whether typed or spoken entries provide a more suitable input modality for these predictive models. Additionally, we explore whether receiving feedback is positively evaluated and which types of feedback students prefer.

**Method:**

In a two-week observational study, N=100 university students (aged 18 years and older) will be recruited and randomly assigned to one of two groups (speaking vs. typing). Following a baseline assessment, participants will submit daily journal entries and annotate them using reflective questionnaires on emotional well-being, stress, and journal topics. This information will be presented to participants as personalized feedback. Additionally, the performance of NLP models in predicting emotional well-being from journal entries will be evaluated separately for the two groups.

**Expected results:**

We expect that emotional well-being can be predicted from journal entries using NLP, with transcribed entries yielding higher accuracy than typed entries. We also expect the feedback to be well-received.

**Discussion:**

This study explores an accessible and engaging journaling application for monitoring and providing feedback on emotional well-being. It addresses several challenges in e-health research (e.g., high dropout rates, low user engagement). If this innovative approach yields strong user engagement and predictive performance, future work should evaluate automatically generated NLP-based feedback in journaling interventions to promote mental health.

**Clinical Trial registration:**

identifier DRKS00034660.

## Introduction

1

University students in Germany experience high levels of emotional distress, with 37% reporting emotional exhaustion [1]. Emotional exhaustion is a key risk factor for mental disorders and contributes to high dropout rates in higher education [2]. Stress plays a major role in deteriorating well-being [3], increasing the risk of mental health disorders [4], and impairing academic performance [5]. Additional factors such as poor physical health, sleep problems, anxiety, and loneliness further aggravate vulnerability [1]. Despite available interventions, such as Cognitive Behavioral Therapy (CBT) [6] and mindfulness practices [7], many students lack awareness and effective coping strategies [8, 9].

Journaling represents a low-cost, accessible, and increasingly popular practice among students, with social media trends further enhancing its appeal. Empirical evidence indicates that journaling can reduce anxiety and depression [10, 11], increase resilience [12], and foster acceptance of negative emotions [13]. For students, journaling has shown benefits in reducing stress [14], improving motivation [15], and enhancing academic performance [16]. However, effects vary depending on journaling type, duration, and population [17]. Journaling can also serve as a tool for monitoring emotional well-being. Traditional self-report instruments capture only limited aspects of subjective experience, while journaling allows for a richer and more ecologically valid picture of daily emotions and stressors [18]. This makes digital journaling particularly suitable for longitudinal monitoring in naturalistic settings. Compared to social media data, which has increasingly been used for mental health prediction [19], journaling allows for greater control over timing and context, as well as structured linkage to daily self-reports, providing a ground truth that has been noted as a persistent challenge in social media-based approaches [20]. Additionally, journaling carries a dual role, serving both as a monitoring tool and as an intervention shown to contribute positively to mental health.

Journaling apps are among the most downloaded mental health apps [21, 22]. Features typically include logging of text entries, mood tracking, reflection prompts, and visualization of entries. Some apps incorporate AI features such as chatbots or automated text analysis, but these remain rare and lack scientific validation [23]. To date, few apps have been tested in controlled studies, and evidence on effectiveness and user preferences is scarce [24, 25].

NLP enables automatic assessment of emotions from text. Applications include monitoring depression severity [26], detecting suicidal tendencies [27], and tracking stress [28]. Transformer-based models such as BERT or RoBERTa are state-of-the-art for sentiment analysis and mental health prediction tasks [29–31]. However, research on NLP applied to journaling data is limited. Existing work has mostly used lexicon-based methods [32, 33] or simple polarity classification [34], which fail to capture nuanced emotional states. No studies have yet applied advanced NLP architectures to journal data. This is furthermore hindered by data scarcity. Available datasets are small, predominantly in English, and lack continuous well-being labels or multimodal entries [35, 36]. German-language data are not publicly available. However, transfer learning offers a way to address these limitations by fine-tuning pre-trained models on small, domain-specific datasets [37, 38].

Input modalities are of further concern, as digital journal entries may be spoken or typed nowadays. This may influence the linguistics, as well as the model performance, as written text is more deliberate and structured [39], while spoken language contains paralinguistic cues such as prosody and pitch that can enhance emotion recognition [40, 41]. A previous study suggests that written text and transcribed speech may yield different prediction accuracies [42], but substantial research on the effect of the input modality on model performance is missing; especially in the context of emotional expression, such as in journaling.

Feedback on the journaling content takes this digital intervention one step further, as feedback on emotional well-being can promote self-awareness, reflection, and behavior change [43, 44]. However, existing apps mostly provide simple statistics, and little is known about which feedback formats are most effective or preferred by students. Personalized feedback is also associated with improved adherence to digital health interventions [45]. Adherence, however, is further moderated by individual self-control, with higher dispositional self-control linked to stronger health behavior adherence [46]. Offering flexible input modalities (typing or speaking) may lower barriers and improve engagement [21]. Consequently, when aiming to promote consistency in journaling, the individual self-control, as well as the input modality, should be under further research.

## Research questions and hypotheses

2

Building upon the illustrated gaps in current research, this study investigates the potential of NLP applied to digital journaling data with the aim of monitoring and supporting students’ emotional well-being, while generating individualized feedback on the journaling content and evaluating the students’ preferences.

Primarily, we hypothesize that (RQ1) emotional well-being and stress levels can be predicted from journaling entries using NLP. Prediction accuracy is expected to be higher for spoken entries (transcribed speech) compared to typed entries. Secondly, we hypothesize that (RQ2) the participants will evaluate the individualized feedback positively, indicating its acceptability and potential to foster reflection and compliance. Thirdly, we expect (RQ3) higher *state self-control* and *trait self-control* to be associated with greater adherence to the study protocol, and will be negatively correlated with dropout rates.

Furthermore, we will undergo (RQ4) an exploratory analysis of the improvement of the students’ emotional well-being over the study period, including the difference when typing vs. speaking the journal entries. Lastly, (RQ5) the predictive performance of NLP models will be compared to that of human experts (psychotherapists and clinical psychologists) in an exploratory manner to gain a practical perspective on the models’ performance. If RQ1 and RQ2 should hold true, future work should proceed to explore the usage of NLP to provide feedback automatically.

## Materials and method

3

The study was approved in September 2024 by the Ethics Committee of the Medical Faculty of the Eberhard Karls University and the University Hospital Tuebingen (Ref. No. 464/2024BO2, [name]) and complies with the latest version of the Declaration of Helsinki [47]. The study was registered in July 2024 (16.07.2024) in the German register for clinical trials (DRKS-ID: DRKS00034660).

### Design

3.1

The study is a two-week observational study with an exploratory approach that uses NLP to explore the applicability of NLP-based analyses of journal entries for monitoring students’ emotional well-being and giving individual feedback. For this purpose, we will analyze the usage of spoken vs. typed journal entries for identifying mood and stress and determine which types of feedback are favored. In more detail, the study will investigate which type of input modality performs better in predicting the students’ emotional well-being using self-labeled journaling entries as ground truth. An overview of the study design is shown in Figure 1; further procedural details are provided in Section 3.3.

**Figure 1 F1:**
[figure not shown]
Overview of the study design.

At the start of the study, participants are randomly assigned to one of two groups: one group records voice messages (audio journals), while the other types their journal entries. We aim to recruit N=100 students aged 18 years or older. Once the technical setup and baseline assessment are completed, participants will provide daily journal entries and complete reflective questionnaires in their everyday lives. These questionnaires will capture information on emotional well-being, stress levels during the day, as well as state self-control, and the topics addressed in the journaling entries. All questionnaire evaluations are considered to be ground truth values, which means that they are the actual reference values for training and evaluating the models. To enhance motivation and facilitate reflection, participants will receive personalized and comprehensible feedback based on their data at the end of the 14-day period. This feedback is derived exclusively from the collected self-report data and does not incorporate any NLP-based analysis to avoid the risk of misinformation. As a final step, participants will be asked to complete a questionnaire that evaluates the feedback document. Additionally, focus group sessions will be held with voluntary participants to obtain qualitative insights into their experiences and study-related feedback (see Section 3.6). Lastly, to contextualize the performance of the NLP models, their predictive accuracy will be compared to that of human experts (psychotherapists and clinical psychologists), thereby providing a practical benchmark for model evaluation (see Section 3.7). No pilot phase will be conducted.

### Participants and recruitment

3.2

Eligible participants will be university students who (a) are at least 18 years of age, (b) possess an internet-enabled smartphone (iOS or Android), and (c) demonstrate adequate proficiency in German, defined as fluent comprehension and production in both spoken and written form. Exclusion criteria are intentionally kept to a minimum to promote broad accessibility. Participants will be excluded only if they are experiencing an acute mental health crisis that necessitates immediate clinical intervention (e.g., acute suicidality).

To minimize participant attrition, several incentive mechanisms will be implemented: (1) all participants will receive individualized feedback upon completion of the 14-day study period; (2) participants who successfully complete the study will be compensated with a €10 voucher redeemable at various online retailers; (3) three additional €50 vouchers will be allocated by lottery among participants within the upper 50% of compliance; and (4) psychology and cognitive science students at the University of Tuebingen will be eligible to obtain university-internal credits.

A non-probability convenience sampling strategy is applied. Recruitment will be carried out through several complementary channels. Primary outreach will occur via university-wide email distribution lists at the University of Tuebingen, where psychology and cognitive science students will be explicitly informed that participation qualifies for university-internal credits. Students from all other disciplines will likewise be eligible and encouraged to participate. Additional on-campus recruitment will be conducted through the display of posters in university buildings. Digital recruitment will include dissemination of study information via the official social media account of the University Hospital Tuebingen and the extension of outreach to students at other universities through targeted posts in messenger-based student groups.

During recruitment, participants will be directed via QR code to the study homepage,^1^ where they can access detailed study information and complete the online registration. Figure 2 provides an overview of the registration process. Participants accessing the registration link will first be asked to confirm that they meet the eligibility criteria; individuals who do not meet these criteria will not be able to proceed. Eligible participants will then provide informed consent by affirming the relevant checkboxes. Using the contact information provided, the study team will send an email containing a personalized QR code directing participants to download a GDPR-compliant messenger service, which will be used to maintain contact with participants throughout the study and to manage data collection. The messenger service facilitates secure, direct communication between participants and the study team, allowing participants to submit individual inquiries via chat, which will be answered on a daily basis. The email will also include an instructional video guiding participants through the installation process and explaining the app’s functionalities. The personalized QR code grants each participant access to a unique user account linked to an individual identifier within the app. Once the application has been installed and activated, the participant will be formally enrolled in the study.

**Figure 2 F2:**
[figure not shown]
Registration process.

### Procedure

3.3

Upon completion of enrollment, participants will be welcomed by the study team within the app and prompted to complete the baseline assessment questionnaires. For this purpose, they will receive an individualized link via the messenger service to an online survey hosted on the SoSci Survey platform^2^, which can be accessed through their smartphone browser. The link will contain each participant’s unique code to ensure accurate data assignment. The survey will cover demographics, education, general well-being, mental health, stress, and dispositional self-control, and is expected to take no longer than 10 to 15 min to complete. Subsequently, participants will be randomized into two groups using block randomization with randomly varying block sizes of 4, 6, and 8 to ensure approximately equal distribution. To generate the list of group assignments, the tool Sealed Envelope [48] is used. Participants are then assigned based on their registration sequence. The type group will be instructed to consistently type their journal entries, whereas the speak group will be instructed to record their journal entries as voice messages via the messenger service. In order to establish a “neutral voice” baseline for each participant in the speaking group, they will be asked to read standardized text snippets from the literature on voice assessment.^3^ These snippets are designed to avoid eliciting emotion or cognitive load.

During the 14-day study phase, participants will be asked to record a daily journal entry as a (voice) message in the messenger service app, sharing their “high- and low-lights” of the day by either typing or speaking according to their group assignment. They will receive a notification via the messenger service around 6 p.m., but the assessment may be completed at any time during the remainder of their day. Immediately after creating the journal entry, participants will be asked to complete a short reflective survey on the SoSci Survey platform, accessed via an individualized link provided in the reminder message. Since the links will be personalized, all reminders will be sent individually and manually by the study team. The sequence—first journaling, then completing the questionnaire—is chosen to ensure that participants can report naturally on topics they consider relevant, without potential bias introduced by answering questionnaires beforehand. All questionnaire scores will serve as ground truth reference values for training and evaluating the NLP models. The total time required for journaling and survey completion is expected to be approximately 5–10 minutes per day. Each daily data point will include a journal entry, three emotional well-being metrics, a daily stress level, a measure of situational self-control, and a list of topics mentioned in the journal entry. To enhance compliance, the study team will monitor on a daily basis whether participants have completed the required assessment. If an assessment is missed or remains incomplete from the previous day, a reminder will be sent in the afternoon notifying the participant of the missed entry. The reminder will also include a brief question regarding the reason for the omission, along with an encouragement to complete the assessments on subsequent days. After the two-week study period, participants will receive individualized feedback based on their journal entries and questionnaire responses (see Section 3.5 for more detail). Providing it once at the end of the study was intended as an incentive to complete the two weeks. As a final step, participants will be asked to complete a feedback questionnaire to provide direct evaluations of their study experience. In addition, focus group sessions with voluntary participants will be conducted to further explore participant perspectives (see Section 3.6 for further details).

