#### Daily journaling

3.4.2

During the 14-day study period, participants will be prompted each evening via the messenger service to record a voice message reflecting on the day’s highlights and lowlights. The standardized instruction will be: “What were your high- and lowlights of the day? How did they make you feel and why?” This prompt is intended to facilitate reflection on both positive and negative experiences. In contrast to stream-of-consciousness instructions (e.g., “Write about your day”), which may yield brief responses, this question is expected to elicit more elaborated entries. By addressing overall emotional well-being, it allows for a broad spectrum of emotions to be captured, rather than restricting the focus to a single emotional dimension as in approaches such as gratitude journaling or expressive writing. No constraints will be imposed on entry length, thereby enabling participants to provide responses of natural scope without artificial extension.

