#### Handling of missing data and dropout

4.3.1

Incomplete daily records will not be used for analysis. Specifically, if a participant provides only a journal entry or only a daily questionnaire for a given day, that day’s data point will be excluded from the dataset. Missing data will not be imputed, as journal entries and subjective reports cannot be reliably reconstructed. Instead, the extent and patterns of missingness will be explored descriptively to assess whether data are missing at random or show systematic trends (e.g., participant characteristics, or study phase). Participant dropout will be recorded, including the timing and, where possible, reasons for discontinuation. Dropout has been accounted for in the sample size calculation.

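### The survey link appears to reach participants before the journal is written, so the journal-first order rests on an instruction alone, and the stated rules would accept a survey-first day as a valid RQ1 pair

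*Protocol article*

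**What the plan says.** Section 3.3 (Procedure) sets the daily routine. On timing: "They will receive a notification via the messenger service around 6 p.m., but the assessment may be completed at any time during the remainder of" the day. On order: "Immediately after creating the journal entry, participants will be asked to complete a short reflective survey on the SoSci Survey platform". The survey is "accessed via an individualized link provided in the reminder message", and on how these messages go out the article adds: "Since the links will be personalized, all reminders will be sent individually and manually by the study team". The reason given for the order is that "participants can report naturally on topics they consider relevant, without potential bias introduced by answering questionnaires beforehand".

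Section 3.4.2 (Daily journaling) confirms what the evening message asks for: "participants will be prompted each evening via the messenger service to record a voice message".

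Three rules decide whether a day counts. The daily monitoring in section 3.3 looks at whether the assessment was completed. Section 4.2.4 defines compliance as completion of both parts on a day. Section 4.3.1 (Handling of missing data and dropout) states that "if a participant provides only a journal entry or only a daily questionnaire for a given day, that day’s data point will be excluded". None of the three refers to which part came first.

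**The concern.** The order is a safeguard that the protocol chose for a stated reason. The survey shows mood, calmness and stress items and a list of eleven topics (section 3.4.3). Its mood and stress scores are the targets that the RQ1 models are trained and tested on. If a participant answers those items and then journals, the text may take up what was just rated. Text and label would then be linked partly through the questionnaire, and RQ1 accuracy could look better than it would for an unprompted entry.

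The delivery works against the safeguard. A participant who already holds the link can open the survey first, on a separate platform from the messenger, and nothing described in the article would prevent or flag it. Randomisation does not settle the matter for the typed-versus-spoken comparison, because the order of completion is behaviour after assignment. Even if reversals were equally common in both groups, the claim that well-being can be predicted from the entries would be affected. No pilot phase is planned (section 3.1), so reversals would not come to light before data collection.

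**Working it through.** **Step 1. Which message carries the link?** Section 3.3 describes two kinds of recurring message.

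- The notification around 6 p.m., which goes to everyone and prompts the journal.
- An afternoon message about a missed or incomplete previous day, which goes only to those who missed something, asks why, and encourages completion on later days.

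The second cannot be the routine route to a daily survey. The Discussion (section 5) also uses both notification and reminder for the daily prompt. The link therefore most plausibly travels in the 6 p.m. message. This is an inference; the article does not say so outright.

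**Step 2. What enforces the order?** The participant is asked to do the survey straight after the entry. No passage says that the link is withheld until the entry arrives, or that the survey checks for it.

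**Step 3. What would happen to a survey-first day?** Suppose the survey is done at 6 p.m. and the entry is sent at 11 p.m. the same day.

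- Monitoring (3.3): both parts present, so complete.
- Compliance (4.2.4): both parts done that day, so scored 1.
- Exclusion (4.3.1): neither part missing, so retained.

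As the rules are written, the day becomes a training or test pair for RQ1.

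**Step 4. Could reversals be identified afterwards?** The individual feedback lists entries with date and time (section 3.5), so journal times are held. The article does not say whether the survey platform's start times are kept.

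**Step 5. What would excluding reversed days cost?** Inputs from section 4.1: target D = 500 data points per group, d = 14 days, dropout r = 0.28.

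- The plan's own figure: N = D / (d × (1 − r)) = 500 / (14 × 0.72) = 49.6, rounded to 50 per group. It reproduces.
- Expected yield: 50 × 14 × 0.72 = 504, a margin of 4 over the target.

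The documents give no share of reversed days. For assumed shares p, the yield is 504 × (1 − p), and the number per group needed to restore 500 is 500 / (14 × 0.72 × (1 − p)), rounded up:

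| Assumed share reversed | Data points left per group | Participants per group for 500 |
|---|---|---|
| 5% | 479 | 53 |
| 10% | 454 | 56 |
| 20% | 403 | 63 |

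Any of these shares takes the yield below target, which favours prevention over later exclusion.

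**The case against.** The article states the order, the instruction and the reason. As a condensed account, it may leave gating or a time-stamp check to a fuller document. That stands against saying that the order is unchecked; the fair statement is that no check is described. It does not remove the point, because placing the link in the reminder message is stated procedure.

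The survey itself favours the intended order: it asks for topics mentioned in the entry and for self-control while journaling, which presuppose a finished entry. Participants also know the items after the first day, whichever order they follow. Both facts probably limit the problem, and a gate cannot remove that familiarity.

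A reader might go further in three ways that the document does not support.

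- **A long gap makes text and label describe different states.** Section 3.4.3 adapts the mood and stress scales to the whole past day, to match entries that also cover the whole day. A few hours between the two parts on one evening changes little.
- **Surveys completed the next afternoon enter as valid pairs.** The afternoon message encourages later days, not backfilling, and completion is confined to the remainder of the same day.
- **The typed-versus-spoken comparison is biased.** Nothing shows that one group would reverse the order more often. Numbers can only be assumed: with a text–score correlation of 0.40 on journal-first days and 0.55 on survey-first days, and reversal shares of 10% and 30%, the groups would differ by about (0.30 − 0.10) × (0.55 − 0.40) = 0.03. For scale, with 504 entries per group, r = 0.40 and entries treated as independent, the standard error of a difference in correlations is about 1.41 × (1 − 0.40²) / √504 = 0.053, a 95% half-width of about 0.10. Clustering within participants would probably widen it. The assumed shift is smaller than that noise.

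**Conclusion.** The point holds as a gap between a safeguard and its delivery. The protocol names bias from answering the questionnaire first as something to avoid, then appears to hand out the questionnaire link with the journal prompt and states only completeness rules, which a survey-first day would pass. This rests on reading the reminder message as the evening prompt, which is the natural reading but is not stated.

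The size of the effect is unknown. The document does not support a claim that reversals will be frequent, that RQ1 accuracy will be inflated by any given amount, or that the groups will differ. This is a worthwhile, inexpensive improvement to the procedure and does not show that RQ1 is invalid.

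**What to change.** 1. **Prevent reversals.** Make the first survey page a gate that asks whether today's entry has been sent and, if not, asks the participant to send it before continuing. Alternatively, send the individualized link only once the entry has been received. The article should state which message carries the link.
2. **Describe what remains.** Compare journal time stamps with survey start times, after confirming that the survey platform logs them. Report the number of reversed-order days by group.
3. **Test sensitivity.** Keep all complete pairs in the main RQ1 analysis and repeat it without the reversed-order days. Routine exclusion is not advisable: the margin over the target is 4 data points per group, and if reversals did differ by group, excluding them would select days differently in each.

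The cost is one extra survey page, or one further message per participant per day from a team that already sends messages by hand, plus a small additional analysis. Releasing the link after receipt is the more laborious option, because staff would have to respond to entries through the evening. The gate page avoids this but still relies on an honest answer.
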